### Pilot Study

A pilot study randomized 6 eligible participants into 2 groups and tested the logistics of the interventions. Feedback was collected from the participants. The results showed that the chatbot operates smoothly, and participants expressed satisfaction with its performance and interface.

### Statistical Analysis

Intention-to-treat analysis will be performed. The Markov chain Monte Carlo method will be used to impute missing primary and secondary outcomes. Variables to impute the missing values include participants’ background characteristics and baseline values of these outcomes. Chi-square and independent sample *t* tests will be performed to examine the between-group balance of potential confounders at baseline. We will compare between-group differences in primary and secondary outcomes at both T1 and T2. The relative risk, absolute risk reduction, and the number needed to be treated and their 95% CI values will be calculated using Microsoft Excel. Logistic regression for binary variables and linear regression models for continuous variables will be used to test between-group differences in primary and secondary outcomes after controlling for any baseline confounders, with *P*<.20 in between-group comparisons. IBM SPSS version 26.0 and R version 4.3.1 (R Foundation for Statistical Computing) will be used for data analysis, with 2-sided *P*<0.05 considered statistically significant.

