## Methods

### Study Design

This is a partially blinded (outcome assessors and data analysts) and parallel-group RCT to be conducted in Hong Kong, China. Inactive community-dwelling people aged 65 years or more will be randomized evenly (1:1) into either an intervention group or a control group. In the intervention group, the chatbot will measure participants’ SOC related to PA and deliver web-based interventions tailored to their current SOC every week for 12 weeks. In the control group, the chatbot will not measure participants’ SOC but will deliver a standard and non-SOC-tailored web-based intervention every week for 12 weeks. Participants will be interviewed at baseline (T0), after completion of the intervention (T1), and 6 months after T1 (T2). The study was registered at ClinicalTrials (NCT06641492). The study flowchart diagram is shown in Figure 1. We will report this trial in accordance with the CONSORT-EHEALTH (Consolidated Standards of Reporting Trials of Electronic and Mobile Health Applications and Online Telehealth) checklist (Multimedia Appendix 1) [31] and the SPIRIT (Standard Protocol Items: Recommendations for Interventional Trials) checklist (Multimedia Appendix 2).

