### Sample Size Planning

At T0, no participant will meet the WHO-recommended PA level according to the inclusion criteria. We assume that 10% of participants in the control group will meet the WHO-recommended PA level at T2 as there are minimum interventions. A target sample size of 97 per group (194 in total) would allow us to detect a between-group difference of 15% in the prevalence of meeting the WHO-recommended PA level at T2 (25% versus 10%; power=0.80, α=.05, PASS version 11.0 [NCSS Statistical Software]). We conservatively estimate the dropout rate to be 30% at T2. Thus, 139 eligible participants per group (278 in total) are required.

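### The stated imputation predictors omit randomised arm (and the T1 outcomes); followed as written, the T2 difference shrinks in proportion to missing data, to about 10.5 points at the planned 30% dropout

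*Protocol article*

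**What the plan says.** The Statistical Analysis section commits to an intention-to-treat analysis in which missing primary and secondary outcomes are imputed by Markov chain Monte Carlo. It then describes the predictors: "Variables to impute the missing values include participants’ background characteristics and baseline values of these outcomes". Arm is not named. The T1 outcomes are not named either, although they are collected and are compared between groups in the same section.

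The section also says: "The relative risk, absolute risk reduction, and the number needed to be treated and their 95% CI values will be calculated using Microsoft Excel". It does not say how these quantities relate to the imputed datasets. Between-group differences are tested by logistic or linear regression, with "2-sided *P*<0.05 considered statistically significant".

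Sample Size Planning supplies the figures that bear on size. "We assume that 10% of participants in the control group will meet the WHO-recommended PA level at T2", and the trial is sized to "detect a between-group difference of 15% in the prevalence of meeting the WHO-recommended PA level at T2". The intervention rate is thus taken as 25%, and the calculation aims for 80% power at an α of 5%. On missing data: "We conservatively estimate the dropout rate to be 30% at T2". This takes 97 per group to 139 per group, allocated 1:1.

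**The concern.** An imputation model has to contain the variables whose relation to the outcome the analysis will estimate. Here that relation is the effect of arm. If arm is absent, the model assumes that participants with the same background and baseline values have the same outcome distribution in either group, and it draws the missing T2 values accordingly. The observed participants carry the treatment effect and the imputed ones, on average, carry none.

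The listed predictors cannot repair this. Randomisation balances background characteristics and baseline outcomes in expectation, so they say nothing about which arm a participant is in.

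At stake is the primary estimate. A real effect of the planned size would be reported as smaller than it is and could be missed. The direction is toward no difference, so this is not a risk of a false claim of benefit.

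**Working it through.** **Inputs from the protocol article.** T2 rates 25% and 10%, power 0.80, α 0.05, 97 per group evaluable, 30% dropout, 139 per group randomised (Sample Size Planning); two-sided testing (Statistical Analysis); 1:1 allocation (Study Design).

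**Inputs assumed here.** Data missing completely at random and equally in both arms; 20 imputations; where T1 is used, T1 rates equal to the T2 rates, T1 observed for everyone, and a T1-T2 correlation of 0.3 or 0.6. The document gives none of these.

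**1. The plan's sample size reproduces.** With the unpooled normal approximation, n = [0.25×0.75 + 0.10×0.90] × (1.960 + 0.842)² / 0.15² = 96.8, so 97 per group. Then 97 / 0.70 = 138.6, so 139. The sample size is not the problem.

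**2. Expected rates when arm is not in the imputation model.** Missing values in both arms are drawn at the common rate (25% + 10%)/2 = 17.5%. With 30% missing:

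- Intervention: 0.7 × 25% + 0.3 × 17.5% = 22.75%
- Control: 0.7 × 10% + 0.3 × 17.5% = 12.25%
- Difference: 10.5 points, which is 0.7 × 15

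In general the difference is (1 − d) × 15 points for a missing fraction d. On the other scales the plan uses:

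- Relative risk: from 25/10 = 2.50 to 22.75/12.25 = 1.86
- Number needed to treat: from 1/0.15 = 6.7 to 1/0.105 = 9.5
- Odds ratio: from (0.25/0.75)/(0.10/0.90) = 3.0 to (0.2275/0.7725)/(0.1225/0.8775) = 2.1

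**3. Power.** If imputed values were treated as observed, 22.75% versus 12.25% at 139 per arm gives about 64%. Under Rubin's rules the between-imputation variance is added and power is lower. Simulation (139 per arm, proper imputation, test on the risk difference; separate runs, hence the ranges) gave:

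| Missing at T2 | Difference, arm omitted | Power, arm omitted | Power, arm included |
|---|---|---|---|
| 10% | 13.5 points | 85-86% | 90% |
| 20% | 12 points | 71-72% | 84-85% |
| 30% | 10.5 points | 51-54% | 79-81% |

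With arm included, the mean difference stays at about 15 points in every row. At 30% missing, an analysis of completers alone has about 80% power, so imputing without arm does worse than not imputing.

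**4. Separating the two omissions, at 30% missing.**

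| Imputation model | T1-T2 correlation 0.3 | T1-T2 correlation 0.6 |
|---|---|---|
| T1 but not arm | 11.8 points, 68% | 13.2 points, 82% |
| Arm but not T1 | 15.0 points, 80% | 15.1 points, 81% |
| Arm and T1 | 14.8 points, 80% | 15.0 points, 86% |

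All rows with arm are free of attenuation to within simulation error. T1 without arm recovers part of the difference, because T1 itself differs between arms, but not all of it. With arm in the model, T1 adds precision when it predicts T2 well.

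**The case against.** The strongest reply is that the sentence says the variables *include* two groups. It does not say that nothing else enters. The source is a condensed journal article, the statistical analysis plan is not shown, and nowhere is arm said to be excluded. That stands as a limit: a reader might infer that the trial will certainly lose its power, and the document does not establish this. But the authors chose to state the predictors, and a statistician working from that sentence would leave out the one variable the comparison depends on.

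A second reply is that 30% dropout is described as conservative. This is fair. At 10% missing, power without arm is still above 80%, although the estimate remains attenuated.

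Several stronger readings are tempting and do not hold:

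- A reader might infer that leaving out T1 causes the bias. It does not once arm is included. A joint model of all outcomes might also bring T1 in without its being listed, though the document does not say so.
- A reader might infer that the baseline value of the primary outcome is a constant and so predicts nothing. That is true only of the IPAQ-SF entry criterion. Physical activity is also measured by accelerometer at T0, on which nobody is screened, and baseline MVPA minutes, a secondary outcome, are already covered by the stated list.
- A reader might infer from the use of Excel that the intervals will be too narrow and the type I error inflated. The document specifies neither a single imputation nor an unpooled table, and a spreadsheet can hold pooled estimates. What stands is that the pooling step for these quantities is not stated.

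**Conclusion.** The concern holds in this form: the stated predictor set names neither arm nor T1, and if followed as written it shrinks the T2 difference by the missing fraction. At the plan's 30% dropout that means about 10.5 points instead of 15, and power of about 51-54% instead of about 80%.

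The attenuation follows from arithmetic on the plan's own rates, given missingness that is completely at random and equal between arms. The power figures also rest on Rubin's rules with 20 imputations and an unadjusted risk difference, whereas the plan tests by logistic regression. The loss scales with actual missingness. The conclusion is conditional on the list being complete, which the wording suggests but does not settle. It merits correction because it touches the primary estimate and the repair is small.

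**What to change.** In the Statistical Analysis section, and in the statistical analysis plan if there is one, state that:

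1. Missing outcomes are imputed separately by randomised arm, or with arm in the imputation model. Masked arm codes suffice, so the blinding of data analysts is unaffected.
2. The T1 outcomes enter the imputation model alongside the background characteristics and baseline values already listed.
3. The relative risk, absolute difference and number needed to treat, with their confidence intervals, are derived from estimates pooled across imputations and not from one completed table.

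If arm and T1 were always intended, one clarifying sentence is enough. The cost is wording and a few lines of code in R, which the plan already names. No new data are needed. The change should be dated before any T2 outcome is analysed by arm; data collection is expected to end in February 2026.

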### Participants and Recruitment

Inclusion criteria are as follows:

Age 65 years or more.Having a Hong Kong identity card.Chinese speaking.Not meeting the WHO-recommended level of MVPA, defined as <150 minutes of moderate-intensity aerobic PA in the past week. The interviewers will assess participants using the validated Chinese version of the IPAQ-SF.Willing to be followed over the phone at T1 and T2.Owning a smartphone.Able to send and read text/voice messages via smartphones.Willing to wear an accelerometer for a week at T0, T1, and T2.

Exclusion criteria include the following:

Blindness or deafnessDiagnosis of major psychiatric diseases (schizophrenia or bipolar disorders) or dementiaScore≥1 in the Chinese version of the Physical Activity Readiness Questionnaire (PAR-Q)Score≤16 in the validated telephone version of the Cantonese Mini-mental State Examination (T-CMMSE) [32]

Participants will be recruited through random telephone calls. Telephone numbers will be selected from up-to-date Hong Kong telephone directories. Trained interviewers will call potential participants over the phone. If there is more than one person in the household who is aged ≥65 years, the one whose birthday is closest to the interview date will be invited for the study to avoid contamination and introduction of extra confounding factors. Interviewers will brief prospective participants about the study and screen their eligibility.

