### Measurements

#### Primary Outcome

Prevalence of meeting WHO-recommended levels of PA (at least 150 minutes of moderate-intensity aerobic PA, at least 75 minutes of vigorous-intensity aerobic PA, or an equivalent combination of MVPA every week) is the primary outcome. PA will be measured using the data provided by the participants in the Chinese version of the IPAQ-SF and from the accelerometers (ActiGraph) at T0, T1, and T2. After completion of the baseline telephone survey and before the randomization takes place, participants will be invited to visit our research office to collect the accelerometers. Onsite, participants will be instructed to wear the accelerometers on their waist (ie, above the right hipbone) with an elastic belt for 7 days, including 5 weekdays and 2 weekends, to collect objective data of PA levels. Participants will be asked to wear the accelerometers at all times except when they are showering or swimming. In addition, participants will be reminded to maintain their daily routine when they are wearing the accelerometers. Participants will visit our research office again 1 week afterward to return the accelerometers and recall their PA levels in the past week by completing the Chinese version of the IPAQ-SF. Similar procedures for collecting and returning accelerometers and completing the IPAQ-SF will be arranged after completion of the telephone survey at T1 and T2. The time on and time off related to accelerometer wearing each day will be recorded, and the data will be used to estimate the time spent in sedentary behavior, light PA, and MVPA. To ensure the accuracy of data that represent the habitual PA levels of participants, data from participants whose accelerometer-wearing time is less than 600 minutes per day will be considered invalid. We will calculate the sedentary time, light PA time, and MVPA time using triaxial cut points. The sedentary time, light PA time, and MVPA time have been defined as <200, <1951, and >1952 counts/minute, respectively, with the epoch length being 60 seconds [33]. The chatbot will automatically record the time spent by each participant with it.

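### Adjustment covariates are picked by baseline tests at P<.20, so baseline activity is left out of the outcome model about 80% of the time, at a modest and avoidable cost in power

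*Protocol article*

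**What the plan says.** In the Statistical Analysis section, chi-square and t "tests will be performed to examine the between-group balance of potential confounders at baseline". Logistic and linear regression models are then "used to test between-group differences in primary and secondary outcomes after controlling for any baseline confounders". The same sentence sets the rule for entry: "after controlling for any baseline confounders, with *P*<.20 in between-group comparisons". No covariate is named in advance for any outcome model.

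Baseline outcome values are used by design in one place only, the imputation model: "Variables to impute the missing values include participants’ background characteristics and baseline values of these outcomes".

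Baseline activity is nevertheless measured in everyone. The Primary Outcome section takes activity from the IPAQ-SF and "from the accelerometers (ActiGraph) at T0, T1, and T2". Under Baseline Survey and Randomization, allocation uses blocks of 8 and no stratification by baseline activity is mentioned, so the design does not balance it either.

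Two further statements bear on the choice of covariate. Sample Size Planning says "At T0, no participant will meet the WHO-recommended PA level according to the inclusion criteria", and Participants and Recruitment sets the inactivity criterion, assessed by IPAQ-SF, as "defined as <150 minutes of moderate-intensity aerobic PA in the past week".

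**The concern.** In a randomised trial every baseline difference between arms arises by chance. A between-arm P value measures how large that chance difference is. It does not show whether the variable predicts the outcome, which is what makes adjustment worthwhile. A useless variable therefore enters one time in five, and a useful one is left out four times in five.

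Two things are at stake. The first is precision: the information in the T0 activity data is used only when the arms happen to differ on it. The second is pre-specification: the set of covariates depends on the data, and in the logistic model so does the conditional odds ratio being estimated.

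This is not a detail left to a statistical analysis plan. The article states a specific rule, and the rule is a poor one.

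**Working it through.** **1. Reproduce the plan's figure.** Inputs from Sample Size Planning: 25% versus 10% at T2, power 0.80, α .05 (two-sided per Statistical Analysis), 30% dropout. With unpooled variance:

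n = (1.960 + 0.8416)² × (0.25×0.75 + 0.10×0.90) / 0.15² = 7.849 × 0.2775 / 0.0225 = 96.8, so 97 per arm.

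Dropout: 97 / 0.70 = 138.6, so 139 per arm. Both figures match. The calculation contains no covariate, so 80% is the power of the unadjusted comparison.

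**2. How often a covariate is used.** Under randomisation the P value of a balance test is uniform, so P(entry) = 0.20 and P(omission) = 0.80 for any one variable. Simulated entry rates were 19 to 20%.

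**3. Binary primary outcome, 97 per arm, 25% versus 10%.** The documents give no baseline-to-T2 correlation, so a range is assumed. Simulated power:

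| Assumed correlation | P<.20 rule | Always adjusted | Forgone |
|---|---|---|---|
| 0.25 | 80.4% | 81.1% | 0.7 |
| 0.5 | 82.5% | 85.8% | 3.3 |
| 0.7 | 83.1% | 90.2% | 7.1 |

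A separate simulation, parameterised by log-odds per SD of baseline activity, gives a similar range: 78.7 vs 79.8% at 0.5, 80.6 vs 83.9% at 1.0, and 82.0 vs 88.6% at 1.5. The losses are 1.1, 3.3 and 6.6 points.

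**4. Why the low end is plausible.** Eligibility cuts off baseline IPAQ-SF activity. Suppose the correlation in an unselected population were 0.5 to 0.7, and eligibility kept the least active 22.2 to 53.3% (the 2020-2022 Hong Kong range in the Introduction). Bivariate-normal range restriction then brings it down to about 0.27 to 0.52. Simulated power near these values was 80.3 vs 81.1% (0.26), 81.0 vs 82.8% (0.34), 82.1 vs 84.5% (0.42) and 81.7 vs 85.7% (0.52), a loss of about 1 to 4 points. The cut-off is applied to the IPAQ-SF, so it restricts accelerometer minutes less directly.

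**5. Continuous outcomes, 97 per arm, effect set to give 80% unadjusted power.** Always adjusting multiplies the residual variance by 1 − r². The sample size per arm that matches 97 unadjusted is 97 × (1 − r²), rounded up.

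| Assumed r | P<.20 rule | Always adjusted | Forgone | 97 × (1 − r²) |
|---|---|---|---|---|
| 0.3 | 80.3% | 82.2% | 1.9 | 89 |
| 0.5 | 82.3% | 89.3% | 7.0 | 73 |
| 0.7 | 86.6% | 97.1% | 10.5 | 50 |

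**6. Type I error under the rule.** For continuous outcomes the simulated rate is 4.6%, 3.6% and 2.5% at r = 0.3, 0.5 and 0.7, against a nominal 5%. For the binary outcome it is 3.9 to 4.4%. With 4,000 runs the Monte Carlo standard error is √(0.05×0.95/4000) = 0.34 points, so 4.4% cannot be told apart from 5%. The direction is conservative because, in the 80% of trials without adjustment, the arms are by selection close on the covariate, while the standard error still carries its full variance.

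**The case against.** Several points on the other side are sound.

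- **The design target is met.** A reader might infer that the trial is underpowered. The documents do not support that: 80% was planned without adjustment, and in the simulations the rule does at least as well as no adjustment. The loss is only against a better analysis.
- **There is no false-positive problem.** A reader might infer that a data-dependent model inflates type I error. The simulations show the opposite, and little effect at all on the binary outcome.
- **The documents do not rank predictors.** That baseline activity is the strongest one is a reasonable expectation, not something they say. The case needs only that it is prognostic.
- **The 80% applies to a single variable.** If several activity measures are screened, at least one enters more often: 1 − 0.8⁴ = 59% for four independent measures, less if they are correlated. Chance still decides which one.
- **Continuous MVPA is not the only informative baseline measure.** Steps, SOC and cognition may also be prognostic. T0 status is constant only on the screening criterion; status defined by accelerometer could vary at T0.
- **The simulated set is simpler than the planned one.** The plan imputes missing outcomes, so 139 per arm would be analysed, with baseline values in the imputation model. The 97 per arm used here is the plan's own evaluable number. Using baseline values for imputation does not put them in the outcome model.

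These points limit the size of the concern. None gives a reason to keep the rule: it had less power than pre-specified adjustment in every scenario with a prognostic covariate.

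The relative risk, risk reduction and number needed to treat computed in Excel beside an adjusted test are a separate reporting matter and are not part of this point.

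**Conclusion.** The concern holds as a modest point of efficiency and pre-specification. The P<.20 rule selects on chance imbalance, omits any given baseline measure in about 80% of trials, and leaves the model open until the arms are compared. It forgoes about 1 to 7 power points on the primary outcome and about 2 to 10 on continuous outcomes.

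These figures rest on assumed correlations (0.25 to 0.7 for the primary, 0.3 to 0.7 for continuous outcomes) and on 97 per arm with the planned 25% versus 10%. For the primary outcome the low end deserves weight, because eligibility restricts baseline IPAQ-SF activity. The omission rate follows from randomisation alone and needs none of these assumptions. The change should be made, but the validity of the trial does not depend on it.

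**What to change.** Before the arms are compared, remove the P<.20 screening and pre-specify for each outcome a model with arm plus that outcome's T0 value, wherever one exists:

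- **Primary outcome:** logistic regression on arm and continuous T0 MVPA minutes, taken from the same instrument that defines the outcome. Both the IPAQ-SF and the accelerometer are named, so the covariate should follow whichever is used. Fix any transformation in advance and choose one that handles zero minutes, which are plausible in an inactive sample; a transformation chosen after looking at skewness would bring back a data-dependent step.
- **Continuous secondary outcomes:** linear regression on arm and the T0 value of the same measure.
- **SOC:** enter T0 stage as a categorical or ordinal covariate.
- **Compliance:** it has no pre-intervention value, so no T0 term applies.

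Any further covariates should be named in advance for their expected prognostic value. Baseline balance can still be described by arm, without significance tests.

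The cost is a change of wording. The T0 measurements are already part of the protocol, and 97 evaluable and 139 randomised per arm remain sufficient because they were computed without adjustment. Recruitment and T1 follow-up are under way, so the change should be dated to show that it came before any comparison of the arms.
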